### Follow-up of patients

Patients will receive standard follow-up according to the Dutch guidelines after the subject has completed the study.

### Premature termination of the study

The study relies on ^124^I PET/CT being predictive for ^131^I-treatment outcome. When 3 patients have been encountered with negative ^124^I PET/CT and positive post-therapy scintigraphy, the main clinical hypothesis can no longer be supported and the study will be stopped.

### Statistical analysis

Patient demographic data, tumor characteristics and data derived from the scans will be described in frequency tables. χ^2^-tests and trend tests (for ordered scales) will be used to determine whether a significant reduction in futile treatments could have been achieved by applying the ^124^I and ^18^F-FDG PET/CT. More in detail: interpretation of both PET-scans will lead to a positive or negative treatment proposal. This will be compared with the actual response on therapy. The definition of a futile treatment will be a negative post ‘blind’ ^131^I therapy scintigraphy. Additionally, accuracy measures such as sensitivity, specificity, positive and negative predictive value will be calculated from this data. Multivariate analysis will be performed whenever appropriate using logistic regression.

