**Methods/Design:**

In a multicenter prospective observational cohort study the hypothesis that the combination of ^124^I and ^18^F-FDG PET/CT can avoid futile ^131^I treatments in patients planned for ‘blind’ therapy with ^131^I, is tested.

One hundred patients planned for ^131^I undergo both ^124^I and ^18^F-FDG PET/CT after rhTSH stimulation. Independent of the outcome of the scans, all patients will subsequently receive, after thyroid hormone withdrawal, the ^131^I therapy. The post ^131^I therapeutic scintigraphy is compared with the outcome of the ^124^I and ^18^F-FDG PET/CT in order to evaluate the diagnostic value of the combined PET modalities.

This study primary aims to reduce the number of futile ^131^I therapies. Secondary aims are the nationwide introduction of ^124^I PET/CT by a quality assurance and quality control (QA/QC) program, to correlate imaging outcome with histopathological features, to compare ^124^I PET/CT after rhTSH and after withdrawal of thyroid hormone, and to compare ^124^I and ^131^I dosimetry.

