### Study design

This study is designed as a nationwide multicenter observational cohort study. The study population includes patients with biochemically suspicion (i.e. increase Tg levels) of recurrence of their previously completely removed thyroid carcinoma without evidence of local recurrence, planned for ‘blind’ therapeutic activity of ^131^I.

The patients to be included in the study should meet the following inclusion criteria:

1. Patients with a history of differentiated thyroid cancer

2. After complete thyroidectomy and ablation of functional remnants with ^131^I.

3. Planned for ‘blind’ treatment with high activity of ^131^I based on biochemically suspected recurrence, defined as a Tg-level above 2.0 ng/ml.

4. Ultrasonography of the neck performed < 2 months prior to inclusion.

If one of the following criteria is met patients will be excluded from the study:

1. Age < 18 years

2. Pregnancy

3. Incapacitated subjects

4. Contrast enhanced CT performed < 4 months prior to inclusion

5. ^131^I therapy performed < 12 months prior to inclusion

6. Indication for other therapy modality (i.e. surgery in case of a positive ultrasonography, radiotherapy, embolization or chemotherapy)

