### Study endpoints

Primary endpoint is the number of futile high dose ^131^I treatments that could have been avoided by implementation of pre-therapy imaging based on post-therapy scintigraphy

Four secondary endpoints were defined: (1) Synchronized QA/QC of ^124^I PET in the Netherlands, (2) correlation of ^124^I PET/CT and ^18^F-FDG PET/CT with histopathological parameters, (3) correlation between ^124^I PET/CT findings during rhTSH and withdrawal combined with low-iodine diet and (4) correlation between ^124^I PET/CT and ^131^I-scintigraphy dosimetry.

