### Sample size calculation

The power calculation is based on the (conservative) assumption that 40% of patients currently undergo a futile treatment. With approximately 50 evaluable patients per year in the Netherlands, we estimate we are able to include a minimum of 100 patients in 3 years. With a sample size of exactly 100 evaluable patients, a two-sided 95.0% confidence interval for a single proportion using the Pearson-Klopper method for constructing the confidence interval (exact binomial CI) will extend 10% from the observed proportion for an expected proportion of 40%.

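### The chi-square test assigned to a reduction in futile 131I treatments cannot show one, because every patient in the single cohort is treated; estimated proportions with exact intervals should replace it

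*Protocol article*

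**What the plan says.** The Study endpoints section defines the outcome as a count within the cohort: "Primary endpoint is the number of futile high dose ^131^I treatments that could have been avoided by implementation of pre-therapy imaging". The Statistical analysis section attaches a test to it: "χ^2^-tests and trend tests (for ordered scales) will be used to determine whether a significant reduction in futile treatments could have been achieved". It then adds detail: "interpretation of both PET-scans will lead to a positive or negative treatment proposal", and "This will be compared with the actual response on therapy". Futility is fixed by the post-therapy scan: "The definition of a futile treatment will be a negative post ‘blind’ ^131^I therapy scintigraphy". Sensitivity, specificity and the two predictive values are to be calculated in addition.

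There is no control group. The Study design section says: "This study is designed as a nationwide multicenter observational cohort study". The abstract says: "Independent of the outcome of the scans, all patients will subsequently receive, after thyroid hormone withdrawal, the ^131^I therapy".

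The Sample size calculation section does not refer to this test. It starts from a futile rate ("The power calculation is based on the (conservative) assumption that 40% of patients currently undergo a futile treatment") and justifies 100 evaluable patients by the width of an exact 95% confidence interval for one proportion. The section on premature termination stops the study once three patients have a negative 124I PET/CT and a positive post-therapy scan.

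**The concern.** A test for a reduction needs two quantities that could differ in either direction. Here one strategy (treat everyone) is observed, and the other (treat only on a positive proposal) is constructed from the same patients. Futile treatments under the second can equal those under the first or be fewer, but never more. A test of no reduction between them therefore mainly measures how often PET would withhold treatment, not whether it withholds from the right patients.

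The sentences that follow can be read as describing another table, the PET proposal against the post-therapy scan. That table is suitable for chi-square, but its null hypothesis is independence of proposal and scan. Rejecting it does not say how many futile treatments would be avoided, which is the primary endpoint, nor how many effective ones would be lost.

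At stake is what a significant result would mean. On neither reading would it establish that PET selection is useful, and the two readings can give opposite answers on the same data.

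**Working it through.** **Inputs.** From the Sample size calculation section: 100 evaluable patients, 40% futile, two-sided 95% interval. Hence 40 futile and 60 non-futile treatments. The article gives no withholding rate for PET, so q below is an assumption and is shown over a range.

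**The plan's own figure.** Exact limits for x=40, n=100: lower = Beta(0.025; 40, 61) = 30.3%, upper = Beta(0.975; 41, 60) = 50.3%. These lie 9.7 and 10.3 points from 40%, so the stated 10% reproduces.

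**Reading 1: futile count under treat-all against futile count under PET, each out of 100.** Uncorrected chi-square = N(ad−bc)²/(product of the four margins), with N=200.

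- Uninformative PET, q=40%: 40×0.6 = 24 remain. 200×(40×76−60×24)²/(100×100×64×136) = 5.88, p=0.015. About 60×0.4 = 24 of the 60 non-futile treatments are withheld as well.
- Uninformative PET, q=50%: 20 remain, chi-square 9.52, p=0.002.
- Uninformative PET, q=30%: 28 remain, p=0.073. At q=20%: 32 remain, p=0.24.
- Selective PET that avoids 13 of 40 futile treatments and withholds no effective one: 27 remain. 200×(40×73−60×27)²/(100×100×67×133) = 3.79, p=0.0515.

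The threshold is 14 avoided of 40 (40 v 26, p=0.035), which is 35%.

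Simulation of an uninformative PET (40,000 trials, n=100, futile probability 0.4, withholding independent of the post-therapy scan) gives these rates of significance at the two-sided 5% level:

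| q (assumed) | Reading 1, unpaired | Reading 1, exact McNemar | Reading 2, proposal by scan |
|---|---|---|---|
| 10% | 0% | 21% | 4.8% |
| 20% | 3% | 82% | 5.1% |
| 30% | 36% | 98.5% | 5.0% |
| 40% | 80% | 99.9% | 4.9% |
| 50% | 97% | 100% | 5.2% |

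Pairing does not cure the problem. All discordant pairs fall on one side, so six avoided treatments are enough (2×0.5⁶ = 0.031).

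**Reading 2: PET proposal by post-therapy scan, N=100.** The level is correct, as the last column shows. The test is blind to direction:

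- Positive scans 36 treat / 24 withhold; negative scans 14 treat / 26 withhold: 100×(36×26−24×14)²/(60×40×50×50) = 6.0, p=0.014.
- Positive scans 24 treat / 36 withhold; negative scans 26 treat / 14 withhold, so that PET withholds mainly from the wrong patients: 100×(24×14−36×26)²/(60×40×50×50) = 6.0, p=0.014.

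**The two readings on the same data.** The uninformative PET at q=40% withholds 16 of 40 futile and 24 of 60 non-futile treatments. Reading 1 gives p=0.015. Reading 2 gives (16×36−24×24) = 0, so chi-square is 0. The selective PET (13 of 40, 0 of 60) gives p=0.0515 on Reading 1, but 100×(13×60−27×0)²/(40×60×13×87) = 22.4 on Reading 2, p<0.001.

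**The case against.** The strongest reply is that the article itself points to Reading 2: straight after naming the test it describes comparing proposal with response. On that table chi-square is valid and an uninformative PET is significant in only about 5% of trials. This stands. A reader might infer from Reading 1 that any random PET would pass the planned test. The document does not support that, because it does not fix that table. Even on Reading 1 the unpaired test passes a random PET in 0%, 3% and 36% of trials at 10%, 20% and 30% withheld.

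A second reply is the three-patient stopping rule. If every negative proposal implies a negative 124I PET, the chance of at most two discordant patients among 60 at 40% random withholding is about 4×10⁻¹¹. The scenarios with 24 of 60 effective treatments withheld would almost certainly be halted. This also stands as a limit on practical harm. But the rule is keyed to 124I alone while the proposal uses both scans, and it does not enter the test.

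Third, the planned sensitivity and specificity already contain the needed quantities, so it would be too strong to say that the trial cannot answer its question. It can, but from those estimates and not from the test named for the purpose.

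Finally, a full protocol or analysis plan may define the table and null hypothesis. Their absence from an article is not the point raised here. The article states both a test and what it is meant to show, and the two do not match on either reading.

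**Conclusion.** The concern holds in a limited form. In a single cohort where all patients are treated, the named chi-square and trend tests cannot show a significant reduction in futile treatments. On the count comparison the samples are nested, the difference has only one possible sign, and the result depends on how often PET withholds: significance needs at least 14 of 40 avoided, whether or not PET is informative. On the proposal-by-scan table the test is sound, but it answers a question about association without regard to direction, not the primary endpoint.

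The figures rest on the article's 40% and 100 patients, and on assumed withholding rates and accuracy values that the article does not give. The documents do not support the inference that the study would probably end with many effective treatments withheld and still claim success, given the stopping rule and the planned accuracy measures. Pre-set success limits for both proportions are a possible design choice, and this finding does not make them a requirement.

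**What to change.** In the Statistical analysis section, replace the chi-square as the analysis of the primary endpoint with estimation by the exact method already used for the sample size. Report:

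- the proportion of futile treatments avoided: negative proposals among patients with a negative post-therapy scan, and the same number over all patients;
- beside it, the proportion of non-futile treatments wrongly withheld: negative proposals among patients with a positive post-therapy scan.

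Give each with its denominator and exact 95% interval. Keep chi-square, if at all, as a descriptive test of association between proposal and scan, with the direction stated.

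The cost is wording only, as the data are already planned. The p-value for a reduction is lost. Mid-range proportions within the subgroups will be less precise than the stated 10 points: 20 of 40 gives 33.8% to 66.2% (half-width 16.2 points), and 24 of 60 gives 27.6% to 53.5% (half-width 13.0). A wrongly withheld proportion near zero is estimated more tightly: 2 of 60 gives 0.4% to 11.5%.

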## Discussion

Since ^124^I has become available for PET scanning, the interest for its use in DTC has been high. More and more studies addressed its potential use in these patients. Furthermore, it is well known that during dedifferentiation of DTC, its tumor cells may become FDG avid and multiple studies have correlated ^18^F-FDG PET/CT with aggressiveness of DTC and the loss of iodine avidity. To our best knowledge no studies however addressed in a large prospective cohort of patients with recurrent thyroid cancer the additional value of these scan modalities in the prevention of futile ^131^I therapies. This is of great clinical importance as a futile ^131^I treatment is costly and not without short- and long-term side effects and should therefore be restricted to those who will likely to benefit from this treatment.

### Trial status

The Medical the Ethics Board of the Netherlands Cancer Institute approved the study for all participating centers. Subsequently, this approval has been checked by all participating centers. The study is recruiting patients Since December 2012. The estimated length of the study is four years.

## Abbreviations

123I/124I/131I: Iodine-123/Iodine-124/Iodine-131; DTC: Differentiated thyroid cancer; LID: Low-iodine diet; MBq: Megabecquerel; ml: Milliliter; mSv: Millisievert; ng: Nanogram; NIS: Sodium/iodide symporter; PET/CT: Positron emission tomography/Computed tomography; rhTSH: Recombinant human thyroid stimulating hormone; RT: Radiotherapy; Tg: Thyroglobulin; TSH: Thyroid stimulating hormone.
